**Figure 1 Fig1:**
[figure not shown]
**Schedule of the CORRA study.** CORRA: Comparison of the efficacy and safety of two starting dosages of prednisolone in early active rheumatoid arthritis, DMARD: disease-modifying antirheumatic drug, MTX: methotrexate, PRED: prednisolone.

**Table 2 Tab2:** **Scope of study visits and assessments of the CORRA study**

	Physical examination, DAS28, laboratory, safety assessment	Radiographs of hands and feet	Patient global assessment, functional capacity, EQ-5D	DXA lumbar spine and hip
Baseline	+	+	+	(+)
Week 5	+			
Week 9	+			
Week 13	+		+	
Week 25	+		+	(+)
Week 53	+	+	+	

CORRA: Comparison of the efficacy and safety of two starting dosages of prednisolone in early active rheumatoid arthritis, DAS28: Disease Activity Score 28, EQ-5D: EuroQol-5D, DXA: Dual-Energy X-ray Absorptiometry.

Allocation concealment is ensured as the randomization code will not be released until the end of the study. Randomization will be performed using blocks with variable block length according to centre. Quality assurance and monitoring will be performed in 100% of data for the inclusion and exclusion criteria, verification of treatment compliance, primary endpoint, and AE. Other trial data will undergo 100% source data verification for 20% of patients.

The treating rheumatologist will record all AE including serious AE and, if necessary, make treatment adjustments in accordance with the protocol. Serious AE are defined as any adverse reaction resulting in any of the following outcomes: a life-threatening condition or death, a significant or permanent disability, a malignancy, hospitalization or prolongation of hospitalization, a congenital abnormality, or a birth defect.

Supervision of the trial will be performed by an independent data and safety monitoring board (DSMB). In case of unexpected safety concerns the biostatistician of the DSMB will perform an interim analysis. The committee will ensure adherence to protocol and provide the funding organization with information and advice.

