### Blinding and statistical methods

All participating rheumatologists and radiologists will be blinded against the interventions, thus assuring blinded assessment of outcome variables.

The primary endpoint is the progression of radiographic damage after one year compared to baseline (measured by the SHS). Analysis will be performed in three steps to compare the three groups (Pl: placebo group; V10: group starting with 10 mg PRED; and V60: group starting with 60 mg PRED). Primary analysis will be conducted by analysis of covariance (ANCOVA) for V60 versus Pl, using baseline values as covariates and 12-month values as dependent variables. In case of a statistically significant result (α = 0.05), a comparison of V10 versus Pl will be performed (α = 0.05). In case of superiority of V10 versus Pl, a non-inferiority test for V10 versus V60 will be performed (α = 0.025), as is shown in Figure 2. A non-inferiority margin of 1.3 SHS points has been selected.

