Of course, these results must be judged by considering other endpoints such as adverse events, clinical response to treatment, and patient-related outcomes. Therefore recommendations should take into account all these results. It is possible, depending on the results, that there may remain sufficient uncertainty and, therefore, that a confirmatory trial may be needed. Nonetheless, the primary endpoint should not be blurred by these short-term results because the focus lies on disease modification as measured by the Sharp score.

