## Abbreviations

AE: Adverse events
CI: Confidence interval
DAS28: Disease Activity Score 28
DMARD: Disease-modifying antirheumatic drug
DRKS: German Clinical Trials Register
DSMB: Data and safety monitoring board
DXA: Dual-Energy X-ray Absorptiometry
ESR: Erythrocyte sedimentation rate
EudraCT: European Union Drug Regulating Authorities
EULAR: European League Against Rheumatism
FFbH: Physical functioning questionnaire Hannover
GC: glucocorticoid
ITT: Intention-to-treat
MTX: methotrexate
Pl: Placebo group
PRED: prednisolone
RA: Rheumatoid arthritis
sd: Standard deviation
SHS: van der Heijde modification of the Sharp score
V10: Group starting with 10 mg prednisolone
V60: Group starting with 60 mg prednisolone.

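### The serious adverse event definition says *reaction* where it should say *event*, so read literally it ties the serious class to a causality judgement

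*Protocol article*

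**What the plan says.** The safety text follows Table 2 in the section on study medication, randomization, and follow-up. It first sets the scope of recording: "The treating rheumatologist will record all AE including serious AE". It then defines the serious class: "Serious AE are defined as any adverse reaction resulting in any of the following outcomes", followed by the outcomes "a life-threatening condition or death, a significant or permanent disability, a malignancy, hospitalization or prolongation of hospitalization, a congenital abnormality, or a birth defect". The abbreviation list gives "AE: Adverse events".

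Three other statements bear on the point:

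- Monitoring covers all data on, among other items, "verification of treatment compliance, primary endpoint, and AE".
- Under Blinding and statistical methods, "All participating rheumatologists and radiologists will be blinded against the interventions".
- In the Discussion, the authors say that "these results must be judged by considering other endpoints such as adverse events".

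The article does not define *adverse reaction*, does not say to which drug the reaction would be, and describes no causality assessment.

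**The concern.** An adverse event is any untoward occurrence in a trial participant. An adverse reaction, in the usual sense of the term, is one suspected to be caused by a drug. Seriousness should rest on outcome alone, with causality judged separately. The definition here merges the two, so an event must count as a reaction before its outcome can make it serious.

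This matters because safety is half of the trial's question. The Background says that a 60 mg start is avoided in most departments because of toxicity, and the design sets that dose against a 10 mg start and placebo. The monitoring board's biostatistician is to run an interim analysis if an unexpected safety problem arises. A harm that nobody expects is the kind most likely to be put down, case by case, to age, comorbidity, the arthritis or the methotrexate that all patients receive. Comparing randomized arms on all serious events does not depend on those individual judgements. A count limited to suspected reactions does.

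**Working it through.** There is no stated figure to reproduce. The check sets the statements side by side and then asks what a literal reading would do to a count.

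**1. Term against definition.** AE is expanded as adverse events, so a serious AE should be an adverse event that meets a seriousness criterion. The definition starts from a reaction instead. The term and its definition disagree.

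**2. Recording rule against definition.** The recording sentence carries no causality condition and places serious AE inside all AE. Reactions are also a subset of events, so the two sentences can both be true. But they imply different boundaries for the serious class: all events with a listed outcome, or only the suspected reactions among them.

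**3. A case followed through.** A patient is hospitalized and the rheumatologist judges this unrelated to treatment.

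- Recorded as an AE? Yes.
- Covered by monitoring? Yes, AE data are checked in full.
- Has a listed outcome? Yes.
- Serious AE under the literal definition? No, because it is not a reaction.

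The event is kept and only its class is lost. Checking data against this definition would confirm the misclassification, not detect it.

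**4. Size.** Let N be the number of patients with an event that has a listed outcome, and r the share judged related. Under the literal definition the tally is N × r and the fraction lost is 1 − r. The article gives neither N nor r, so the loss may lie anywhere from 0% (r = 1) to 100% (r = 0).

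For illustration only, with assumed rates:

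| Assumed share of 450 patients with a serious outcome | N | Tally if 30% judged unrelated | Tally if 80% judged unrelated |
|---|---|---|---|
| 5% | 450 × 0.05 = 22.5 | 22.5 × 0.7 = 15.75 | 22.5 × 0.2 = 4.5 |
| 10% | 450 × 0.10 = 45 | 45 × 0.7 = 31.5 | 45 × 0.2 = 9 |

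The table shows the mechanism. It does not estimate this trial, because the loss is simply the share that was assumed.

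**5. Effect on a comparison of arms.** For two arms, observed ratio = true ratio × (r in one arm ÷ r in the other). If r is the same in both arms, the ratio is unchanged, but the counts and their absolute difference shrink by the factor r. The ratio is distorted only if r differs between arms. The document does not show that it would.

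**The case against.** The strongest reply is that this is one loose noun. No causality scale, relatedness rule or exclusion of unrelated events appears anywhere. The listed outcomes carry no relatedness condition. The term being defined is serious AE, and the sentence before it treats these as part of all AE. The trial commits itself to good clinical practice, and the full protocol may well use the standard definition. On that view, *reaction* simply means *event*.

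Much of this stands, and it limits what can be claimed. A reader might infer that the safety comparison is undercounted and biased by attribution. The document does not support that, for four reasons:

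- All AE are recorded and monitored whatever their cause, so events are not lost; at most their serious label is.
- The rheumatologists are blinded, which limits differing attribution by arm. Recognisable glucocorticoid effects could partly unblind them, but the article does not discuss this.
- Serious AE are not among the listed secondary endpoints, and no analysis of them between arms is set out.
- The Discussion weighs adverse events, the broader category, which the wording does not restrict.

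Nor is the absence of a causality field or of a specified reporting set for the monitoring board a fault. An article may leave such operational detail to the full protocol.

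The reply does not remove the defect itself. The sentence is a stated definition, not a detail left out, and it is wrong as written. If it is only loose, the 30 practices could still read it in different ways.

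**Conclusion.** The definition should be corrected. It conflicts with the document's own term and sets a different boundary from the one that the recording sentence implies. Applied literally, events with a serious outcome but judged unrelated would stay in the AE data without the serious class, and any serious-event count built on the definition could be too low and depend on attribution.

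The conclusion rests on two conditions: that *adverse reaction* carries its usual causal meaning, which the article neither confirms nor denies, and that sites apply the sentence as printed. The size of any undercount cannot be determined from the document. Bias between arms is possible but not shown. The radiographic primary endpoint is unaffected. This is a wording error in a core safety category, worth correcting because the trial asks a safety question and the correction costs almost nothing.

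**What to change.** In the definition, replace *any adverse reaction* with *any adverse event, whether or not considered related to study medication*, and leave the list of outcomes as it is. Count serious events on that definition in the safety summaries by arm. The sentence then agrees with the rule that all AE are recorded.

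The cost is one phrase, plus the same edit to the serious-event form or site instructions if they repeat it. A few more events may be processed as serious. If forms have already been completed under the printed wording, the recorded AE can be checked for listed outcomes and reclassified, since the events themselves should be in the data.

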### Primary outcome parameter

One of the best evaluated and relevant outcome measures in the assessment of RA is the radiographic joint damage as measured by the van der Heijde modification of the Sharp score (SHS) [21]. This score reflects the structural damage caused by the inflammatory joint disease.

Radiographic joint damage, as assessed by the SHS or other scoring systems, correlates with physical function [22], employment status [23], and mortality [24]. The effects discussed in the literature are comparable to the effects assumed for this study. According to the ‘window of opportunity’ concept, reduced radiological damage early in the course of RA leads to a beneficial modification of the long-term outcome. Therefore, the primary outcome parameter will be the progression of radiographic joint damage after one year compared to baseline measured by the SHS.

### Secondary outcome parameter

Secondary endpoints will be: percentage of patients in remission (as defined by DAS28 < 2.6) or in a state of low disease activity (DAS28 ≥ 2.6 and DAS28 < 3.2) both at week 13 and after one year, changes of FFbH at week 13 and after one year, decline in bone mineral density (DXA lumbar spine and hip) at six months compared to baseline, number and overall dose of GC injections, direct costs of treatment over one year, mean MTX dosage, patient global assessment of disease activity, and percentage of patients who switch to biological treatment in cases of inefficacy of conventional DMARD therapy.

Among all secondary endpoints, the DAS28 is the most important since it is a well-established tool used to assess disease activity in RA. In daily routine, it is frequently used to guide therapeutic decision-making. Similarly, the FFbH is a validated tool to measure physical functioning which is considered to be one of the most important prognostic markers in RA [20]. To assess the risk of osteoporotic fractures, the measurement of bone mineral density (done by DXA) is recommended by the German ‘Dachverband Osteologie’. To estimate the economic burden of RA, direct costs of treatment per month over one year will be determined. To take into account the total intra-articular dose of GC, the number and overall dose of GC injections is recorded. As a lower GC dosage may lead to an increase in MTX dosage, the mean MTX dosage will be a secondary endpoint. To provide patients’ perspective of the effects of the different treatment arms, patient global assessment of disease activity is selected as a secondary endpoint. As treatment with biologicals leads to reduced radiographic joint damage that is comparable to the disease modifying effect of GC, the percentage of patients who switch to a biological treatment in cases of inefficacy of conventional DMARD therapy will be assessed as a secondary endpoint. Finally, a secondary analysis of the primary outcome parameter will be performed, adjusting for mean MTX dose, use of biologicals, and mean GC dose during weeks 13 to 52.

### Sample size

It is assumed that progression of radiographic joint damage as measured by the SHS will be the same for both dosage levels of PRED. For sample size calculation we used data from the BeSt-study [9]. We thus assume an effect of 3.7 and a standard deviation of 7.5. Accounting for a 5% dropout rate, the effect will be 3.5. If 150 patients per group are included, a two sided t-test of superiority (α = 0.05) between one of the PRED groups and the placebo group will give a power of >0.95. Accepting a non-inferiority margin of 1.3 (one third of the known placebo-verum difference) for the difference in progression between the PRED groups, the one sided non-inferiority test in step three (at α = 0.025) will give a power of >0.80, if 149 patients per PRED group are included. The significance level of α = 0.025 was chosen according to the European Medicines Agency guidelines [25]. Thus, the final sample size has been set as 150 patients per group.

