## Background

Rheumatoid arthritis (RA) is a chronic disease characterized by inflammation of the peripheral joints leading to disability, impaired functioning, and premature death. Irreversible joint damage may occur very soon after disease onset. The most important treatment strategy is the early use of disease-modifying antirheumatic drugs (DMARD). However, DMARD have a delayed onset of efficacy and side effects may require cessation of treatment.

Glucocorticoids (GC) are fast-acting anti-inflammatory drugs, now also considered as disease modifying because of their ability to decelerate structural damage [1]. Especially during the first weeks of DMARD treatment, GC are frequently used due to the rapid onset of their anti-inflammatory efficacy. However, it is well known that GC may have considerable side effects such as osteoporosis, diabetes mellitus, arterial hypertension, cardiovascular events, glaucoma, tuberculosis, and weight gain [2]. Hoes *et al*. [3] systematically analyzed the literature on reported adverse events (AE) and found the risk of AE to be 43 per 100 patient-years (95% confidence interval (CI): 30 to 55).

There is good evidence of clinical, functional, and structural efficacy for: 5 to 10 mg prednisolone (PRED)/day over two years [4–7]; and initial dose of 60 mg PRED, tapered to low or zero dose over six to eight months [8, 9] given in addition to DMARD [10]. However, in most rheumatology departments a dosage of 60 mg PRED is not used in the treatment of RA due to toxicity concerns. With the common implementation of ’treat-to-target’ strategies [11], including higher doses of DMARD and a more rapid dose escalation, the percentage of patients undergoing concomitant GC treatment over a long period may diminish. Thus, within a treat-to-target setting, lower dosages of PRED taken over a short period may render sufficient disease modification. Usually, a low (<7.5 mg PRED equivalent a day) to medium (>7.5 mg but <30 mg PRED equivalent) [12]) dose GC schedule is thought to provide sufficient benefit [13]. Following the European League Against Rheumatism (EULAR) recommendations [14], the dose is often tapered as rapidly as is clinically feasible [15].

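### The non-inferiority margin of 1.3 SHS points is not one third of the only undiluted effect the protocol gives (3.7/3 = 1.23), so the step-three threshold is about 5% looser than its justification

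*Protocol article*

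**What the plan says.** The Sample size section names one source for its assumptions, "For sample size calculation we used data from the BeSt-study [9"], and draws the planning values from it: "We thus assume an effect of 3.7 and a standard deviation of 7.5". It then dilutes the effect: "Accounting for a 5% dropout rate, the effect will be 3.5". For the comparison of the two prednisolone groups it assumes that "progression of radiographic joint damage as measured by the SHS will be the same for both dosage levels of PRED", and sets the limit: "Accepting a non-inferiority margin of 1.3 (one third of the known placebo-verum difference"). It claims power above 0.80 for that test, one-sided at α = 0.025, with 149 patients per prednisolone group.

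The section on blinding and statistical methods carries the same number into the analysis: "A non-inferiority margin of 1.3 SHS points has been selected". So 1.3 is the threshold for the third confirmatory step as well as a planning figure. The same section excludes missing values from step three.

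**The concern.** The paragraph gives a rule (one third), an input to the rule (3.7) and a result (1.3), and the three do not agree. A reader cannot tell which was intended: a margin of one third, a margin of 1.3, or a reference difference other than 3.7.

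The margin decides whether the 10 mg start is declared non-inferior to the 60 mg start. Its only stated justification is the fraction of the known effect that may be given up. If the margin exceeds that fraction, a result that just meets it does not carry the assurance the justification implies. The mismatch here runs in the lenient direction.

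**Working it through.** **Inputs.** From Sample size: effect 3.7, SD 7.5, diluted effect 3.5, margin 1.3, true difference 0 between prednisolone groups, 150 per group for superiority, and 149 per group with one-sided α = 0.025 for non-inferiority.

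**Which inputs the plan used.** The superiority power reproduces. The standard error is 7.5 × √(2/150) = 0.866. With the diluted effect, 3.5/0.866 = 4.04, and Φ(4.04 − 1.96) = 0.98. This agrees with the stated value above 0.95, so effect and SD are read correctly.

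**The margin against its rule.**
- One third of the undiluted effect: 3.7/3 = 1.233, which is 1.2 to one decimal.
- Stated margin as a share of that effect: 1.3/3.7 = 0.351, or 35%.
- Difference that would make 1.3 one third: 3 × 1.3 = 3.9. Allowing for rounding of 1.3, the range is 3 × 1.25 = 3.75 to 3 × 1.35 = 4.05, and 3.7 lies outside it.
- Excess: 1.3 − 1.233 = 0.067 points, and 0.067/1.233 = 5.4%.
- Share of 3.7 preserved at the limit: 1 − 0.351 = 64.9%, against 66.7% under the stated rule.

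**Step-three power at each margin.** With SD 7.5 and 149 per arm the standard error is 7.5 × √(2/149) = 0.869. Power = Φ(margin/0.869 − 1.96).

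| Margin | margin/SE | Power |
|---|---|---|
| 1.3 | 1.496 | 0.32 |
| 1.233 | 1.419 | 0.29 |
| 1.2 | 1.381 | 0.28 |

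For 80% power, n per arm = 2 × 7.5² × (1.960 + 0.842)² / margin². This gives 523 at a margin of 1.3 and 883.0/1.44 = 613.2, so 614, at 1.2.

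The choice between 1.3 and 1.2 therefore moves the power by about 0.04. The distance from the stated value above 0.80 is far larger and exists at either margin.

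**What the first two steps add.** Step three is reached only if both prednisolone groups beat placebo. At SD 7.5 and 150 per arm, an unadjusted comparison is significant once the observed difference exceeds about 1.97 × 0.866 ≈ 1.70. A margin of 1.3 is about 76% of 1.70 (1.3/1.70). Passing the two steps shows superiority to placebo; it does not show that two thirds of the 60 mg effect is retained.

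**The case against.** The best defence is the word known. The protocol says it assumes 3.7 but calls the margin's reference the known difference and gives it no separate number. A reference value near 3.9 would make 1.3 correct. This is possible and cannot be excluded from the article. It does not remove the point, because the same paragraph takes 3.7 from the trial it cites and gives no other undiluted value. It does mean that stating the missing figure would be a full remedy.

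It is also fair to say that 0.07 SHS points is little, and that the plan promises a test at 1.3 and not a proof of two-thirds retention. Both stand, and they limit the weight of the point.

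A reader might infer more than the document supports:
- **A larger excess, measured against 3.5.** That figure is the effect diluted for dropout. It suits steps one and two, where missing radiographs are replaced from placebo patients. Step three excludes missing values, so 3.7 is the right comparator.
- **Deliberate rounding in the lenient direction.** The document shows that the figures disagree; it does not show how 1.3 arose.
- **No check against concurrent placebo.** Steps one and two compare each prednisolone group with placebo. What is absent is only an estimate of the share of effect retained.
- **A margin drawn from a regimen that does not carry over.** The Background describes two cited trials together as "initial dose of 60 mg PRED, tapered to low or zero dose over six to eight months", whereas this intervention lasts 12 weeks. The article does not say which arms or which comparison produced 3.7, and any smaller effect for this trial would be an assumption.

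**Conclusion.** The point holds as an internal inconsistency in a confirmatory decision rule. Against the only undiluted effect in the article, 1.3 is 35% and not one third, and the threshold is about 0.07 points (5%) looser than its justification. This rests on 3.7 being the difference meant by the margin statement; a documented reference between 3.75 and 4.05 would resolve it.

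The numerical consequence for the trial is small. It does not make the step-three test invalid, and the mismatch does not account for the shortfall in power. The power figures assume the stated SD of 7.5, a true difference of zero and an unadjusted comparison. Covariate adjustment could reduce the residual SD and raise them, but the article states no smaller SD.

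**What to change.** Choose one of the following and make the Sample size and statistical methods sections agree:
1. Set the margin to 1.2 (3.7/3 rounded down) in both.
2. Keep 1.3 and describe it as 35% of 3.7.
3. Keep 1.3 and state the reference difference actually used, with its source.

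Options 2 and 3 change wording only. Option 1 alters a prespecified decision rule after recruitment has begun, so it needs an amendment made without knowledge of results by arm.

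With any option, restate the step-three power for the chosen margin. On the plan's own inputs that is about 0.32 at 1.3 or 0.28 at 1.2. If a smaller SD was used for step three, state it and justify it. The cost is that the power above 0.80 can no longer be claimed on the figures given.

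Optionally, report as a supportive estimate the share of the V60-placebo effect retained by V10, (Pl − V10)/(Pl − V60), with a 95% interval such as Fieller's. Take all three arms from one analysis set, because missing radiographs are handled differently in step three. This needs no new data. It would be unstable if the V60-placebo difference is small, so it should not serve as a further test.

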**Figure 2 Fig2:**
[figure not shown]
**Statistical analyses procedure of the CORRA study.** CORRA: Comparison of the efficacy and safety of two starting dosages of prednisolone in early active rheumatoid arthritis, Pl: placebo group, V10: group starting with 10 mg prednisolone daily, V60: group starting with 60 mg prednisolone daily.

Statistical analysis will be performed using an intention-to-treat (ITT) approach. It is expected that 12-month results will be missing for less than 5% of the patients (dropout rate). In step one and two, missing radiographs after one year are substituted by randomly selected radiographs of patients of the placebo group (both replacements by the same patient), thus leading to conservative results for the PRED groups. In step three of the test procedure, missing values will be excluded from the analysis. A sensitivity analysis will be done for the effect of the replacement procedure (the random replacement will be repeated several times).

Analysis of the secondary outcome parameters will be performed by ITT using all available data. Continuous characteristics of the groups will be compared using analysis of covariance adjusting for baseline data. Analysis of categorical variables or proportions will be performed using the chi-square test. An additional repeated measures analysis will be done for all quantitative endpoints taken at several time points.

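### The stated step-three power (>0.80 with 149 per prednisolone arm) does not follow from the only standard deviation in the document, which gives 0.32

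*Protocol article*

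**What the plan says.** The Sample size section of the protocol article introduces its inputs in one sentence, with data taken from a cited earlier trial: "We thus assume an effect of 3.7 and a standard deviation of 7.5". The effect is then reduced to 3.5 for 5% dropout. With 150 per group, the power for either prednisolone group against placebo is given as above 0.95.

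For step three the section assumes that "progression of radiographic joint damage as measured by the SHS will be the same for both dosage levels of PRED". The margin is introduced with the words "Accepting a non-inferiority margin of 1.3 (one third of the known placebo-verum difference) for the difference in progression between the PRED groups", and the test is one-sided at α = 0.025. This test, the section says, "will give a power of >0.80, if 149 patients per PRED group are included". It concludes that "the final sample size has been set as 150 patients per group".

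The section Blinding and statistical methods repeats the margin ("A non-inferiority margin of 1.3 SHS points has been selected") and names ANCOVA with baseline as covariate. It expects 12-month results to be missing for fewer than 5% of patients. On these it says: "In step three of the test procedure, missing values will be excluded from the analysis". The article gives no second SD, no SD specific to the prednisolone arms, and no correlation between baseline and outcome.

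**The concern.** The paragraph gives everything needed to compute the step-three power, and the result is far from the figure printed. The figure matters for two reasons. First, the requirement of 149 led to 150 per group; superiority over placebo was already well powered at that size. Second, step three is the formal comparison of the two starting doses, which is one of the trial's two main aims. If the power is much lower than stated, a non-significant step three would be a common result even for two equally effective schedules, and a reader who trusts the printed figure could give it too much weight.

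There is also a smaller problem. Step three is run on patients with observed values only, yet the dropout allowance in the Sample size section touches only the superiority effect.

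**Working it through.** **Inputs** (Sample size section unless noted): SD 7.5; superiority effect 3.5; margin 1.3; true V10–V60 difference 0; one-sided α 0.025 for step three; 149 per arm required and 150 planned. Missing data below 5%, excluded in step three (Blinding and statistical methods). At the upper end of that loss, 150 × 0.95 = 142.5, so about 142 per arm remain.

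**1. The superiority figure reproduces.** SE = 7.5 × √(2/150) = 0.866. 3.5/0.866 = 4.04. Power = Φ(4.04 − 1.96) = 0.98, in line with the stated >0.95. So 7.5 works as the SD for this part of the paragraph.

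**2. The non-inferiority figure does not.** SE = 7.5 × √(2/149) = 0.869. 1.3/0.869 = 1.496. Power = Φ(1.496 − 1.960) = 0.321, or 0.320 with the noncentral t. With 142 per arm it is 0.31.

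**3. Size needed at SD 7.5.** n = 2 × (1.960 + 0.842)² × 7.5²/1.3² = 522.5, so 523 evaluable per arm. Alternatively, 149 per arm gives 0.80 power only for a margin of 2.802 × 0.869 = 2.43.

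**4. The SD that gives 149.** SD = 1.3/(2.802 × √(2/149)) = 4.005. As a check, 2 × 2.802² × 4.0²/1.3² = 148.6, which rounds up to 149.

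**5. Variants at SD 7.5.** One-sided α of 0.05 with 150 per arm gives 0.44. A margin of exactly one third of 3.7, that is 1.23, gives 0.29 at 149 per arm. (At one-sided α of 0.05 an SD of 4.5 would also give 149, but the paragraph fixes α at 0.025, and 4.5 is not in the document either.)

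**6. Covariate adjustment.** To bring a residual SD from 7.5 down to 4.005, baseline must explain 1 − (4.005/7.5)² = 0.715 of the variance, a correlation of about 0.85. A correlation of 0.5 gives power 0.41, and 0.7 gives 0.55.

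**7. Power by SD** (noncentral t, margin 1.3, one-sided α 0.025):

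| SD | 149 per arm | 142 per arm |
|---|---|---|
| 4.0 | 0.80 | 0.78 |
| 5.0 | 0.61 | 0.59 |
| 6.0 | 0.46 | 0.44 |
| 7.5 | 0.32 | 0.31 |

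**The case against.** The strongest reply is that 7.5 was never meant for step three. It is stated beside the effect of 3.7, which is the contrast with placebo. The number 149 is what an SD of 4.0 gives, which suggests a separate SD for the prednisolone arms that was left out of the article. The two values can coexist: with SD 4.0 on prednisolone, a placebo SD of √(2 × 7.5² − 4.0²) = 9.8 gives a pooled 7.5 for the placebo comparison. On that view the planners did not miscalculate.

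This has force. A reader might infer that about 0.31 is the trial's actual power, or that step three will probably fail. The document does not support either inference, because both require 7.5 to hold within the prednisolone arms, and the text does not say that it does. A reader might also infer that ANCOVA cannot close the gap. That is likely if 7.5 is the SD of progression, which is the natural reading. But the text does not label the SD, and the ANCOVA uses 12-month values as the outcome, so the possibility is not strictly excluded.

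The dropout point should also be kept in proportion. At SD 4.0 the power is 0.80 with 150 evaluable per arm and 0.78 with 142, and 142 is the upper end of the expected loss.

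Nor does the article say that a failed step three would count against the low dose. Its Discussion gives no interpretation for that outcome, and it allows that uncertainty may remain and that a confirmatory trial may be needed.

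The reply does not remove the mismatch. A condensed article may omit inputs. Here it prints one SD as the basis of the calculation and a power that this SD does not give.

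**Conclusion.** The point holds as an error in the text as written: the printed inputs give a power of 0.32, not above 0.80. This rests on reading the single stated SD as applying to the V10–V60 comparison, with a true difference of zero, margin 1.3 and one-sided α of 0.025. If an unstated SD of about 4.0 was used, the claim is right to rounding at 149 or 150 evaluable patients per arm, and slips to 0.78 if 5% are excluded. The power falls quickly for SDs between these two values. The document does not show which SD applies, so the conclusion is that the stated power is unsupported by its inputs, not that the trial's power is known to be low. Because this calculation set the sample size, the mismatch has to be corrected.

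**What to change.** In the Sample size section:

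- State the SD used for V10 versus V60, say where it comes from, and justify it if it differs from 7.5.
- Restate the step-three power after exclusion of missing values. If 7.5 applies, it is about 0.31; if about 4.0 applies, it is about 0.78.
- Show the power over the plausible range. With 142 per arm it is 0.78, 0.59, 0.44 and 0.31 for SD 4, 5, 6 and 7.5.
- Add that failure to show non-inferiority in step three is inconclusive and is not evidence that V10 is inferior.

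The cost is a rewritten paragraph and a less favourable stated power. No extra patients are needed.
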